### Randomization and binding

2.5

A completely random design will be used to allocate patients who meet inclusion criteria and sign the informed consent. All the patients will be assigned to the 2 groups randomly in a 1:1 ratio. Patient enrollment, randomization and treatment allocation will be performed by 3 different researchers respectively. Random numbers (from 1 to 60) will be generated by a statistical expert of the Sichuan TCM Evidence-Based Medicine Center before recruitment, and then the numbers will be allocated to the 2 study groups. These numbers will be kept by an independent researcher in an opaque envelope with corresponding treatment allocation. Patients will be given MMD granules or placebo during the treatment period after grouped. Both MMD granules and placebo granules will be produced by Sichuan Green Pharmaceutical Technology Development Co, Ltd to ensure that they are identical in specifications such as appearance, shape, smell. All the patients and researchers (except for who conducting treatment allocation) will be all blind to group number and treatment plan. In case of an emergency, such as adverse events, the randomization number and treatment allocation will be exposed to researchers and supervisors as soon as possible. Therefore, the concealment and blinding of the assignment will be confirmed.

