### Study population and recruitment

2.3

IPF patients will be recruited by respiratory physicians from respiratory clinics at the Hospital of Chengdu University of Traditional Chinese Medicine (Chengdu, China), a national clinical trial and research center of TCM. Subjects will be recruited via all kinds of method like advertisement and doctor referrals. All patients have to get the advice by a specialist in Department of Respiratory Medicine before receiving treatment. All the patients will sign the informed consent before enrollment. Recruitment will last for a year from September 2020 or until the total sample are completed.

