### Sample size calculation

2.4

Calculation of the sample size was based on the primary outcome variable, forced vital capacity (FVC). According to previous study,^[20]^ the mean of FVC in control group was 3.07 L and the standard deviation was 0.71 L after taking Pifenidone. With oral MMD plus Pifenidone, the mean in experiment group was 3.81 L, and the standard deviation was 0.85 L. We employed following formula to calculate the sample size in each group: n *= (μ*_*α*_* + μ*_*β*_*)*^*2*^ *×* *(1+1/k)* *×* *σ*^*2*^*/ (μ*_*2*_*-μ*_*1*_*)*^*2*^, where *σ*^2^ is overall variance, which was estimated as sample variance *s*^2^ just like the formula *s*^*2*^*= (s*_*1*_^*2*^* + ks*_*2*_^*2*^*) / (1 + k)*. The proportion of subjects between the experiment and control groups was set to 1:1 (k = 1). The study was designed to have a power of approximately 90% and 1-side level of significance of 0.05 (a = 0.05, β = 0.1). *μ*_2_, *μ*_1_, *s*_1_, and *s*_2_ are mean and standard deviations in the control and experiment groups respectively. Twenty-three patients are needed in each group based on the formula mentioned above. Considering a 10% of drop-out rate, approximately 26 patients should initially be recruited in each group. In the study, 30 subjects will be recruited in each group actually, with a total of 60 subjects.

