## Discussion

4

There are 2 different theories in TCM and Western medicine about recognition and treatment of diseases. Diagnosis of TCM will combine disease, syndrome, relevant clinical signs and symptoms, with all together to establish a treatment principle. Syndrome differentiation is the core of TCM practice, and we formulate the MMD to treat IPF patients for this study with qi and yin deficiency syndrome.

IPF is a serious global health problem with poor prognosis. Available medications for IPF cannot get the satisfactory results for patients at present. There have been many years of TCM prescription used in adjuvant treatment for IPF in China. MMD is a common formula for the disease.

As we know, this is the first double-blind, placebo-controlled, randomized clinical trial to evaluate the efficacy and safety of MMD plus western medicine in the treatment of IPF. This study will provide a preliminary evaluation of the efficacy and safety of MMD in IPF. Sixty subjects will be recruited in this clinical study. At the same time, they will be divided into 2 groups according to the randomization performed before recruitment. However, there are some limitations in the study. On the one hand, the sample size is too small, which calculated based on previous research, and it may be smaller than it needs. On the other hand, a follow-up period of 24 weeks may be relatively short duration to assess the efficacy and safety of TCM in IPF, a chronic disease.

In conclusion, this study hypothesis that MMD plus Pirfenidone can improve pulmonary function, decrease the time of acute exacerbations and improve quality of life with IPF patients. If the results of the study are positive, it will be possible to give another option in the area of adjuvant treatment with IPF.

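### Allocation without blocks or strata and an unadjusted analysis leave a 60-patient trial open to chance imbalance in baseline severity

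*Protocol article*

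**What the plan says.** Section 2.5 of the protocol article (Randomization and binding) names the method: "A completely random design will be used to allocate patients who meet inclusion criteria and sign the informed consent". It adds that "All the patients will be assigned to the 2 groups randomly in a 1:1 ratio". The list is closed and made in advance: "Random numbers (from 1 to 60) will be generated by a statistical expert", "and then the numbers will be allocated to the 2 study groups". The Discussion confirms the timing: patients "they will be divided into 2 groups according to the randomization performed before recruitment". The rule for dividing the 60 numbers between the arms is not spelled out, and no block or stratification factor appears anywhere.

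Section 2.4 sets the arm sizes: "In the study, 30 subjects will be recruited in each group actually, with a total of 60 subjects". Section 2.3 sets the recruitment window: "Recruitment will last for a year from September 2020 or until the total sample are completed". There is one recruiting hospital.

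Section 2.7 lists FVC% below 50% among the conditions that are evidently exclusions (the list is mislabelled as inclusion criteria) and gives no upper limit. Section 3.2 makes change in FVC and the number of acute exacerbations the primary outcomes. Section 3.6 plans tests of baseline homogeneity, then t-tests or nonparametric tests for measurements and chi-square or Fisher tests for counts. It mentions no baseline covariate.

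**The concern.** A small trial can deal with a strong baseline factor at allocation, by stratifying, or in the analysis, by adjusting. The article states a choice at each stage, and neither choice does so. Calling the design completely random reads as a decision about method, not as a detail held over for the full protocol.

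Eligible patients can range from an FVC% of 50% upward. If baseline severity is related to the outcomes, a chance excess of sicker patients in one arm makes the result harder to interpret. Change from baseline deals with part of this for FVC. The exacerbation outcome has no baseline value of its own in the article, so the stated analysis has nothing to absorb such a difference. Testing baseline homogeneity may reveal an imbalance but does not correct it.

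At stake are the precision of the estimate and how far readers will trust it. The validity of the randomisation is not in question.

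**Working it through.** **1. The plan's own arm sizes.** Inputs from section 2.4: means 3.07 L and 3.81 L (difference 0.74 L), SDs 0.71 L and 0.85 L, power 90%, α 0.05, k = 1.

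- Pooled variance: (0.71² + 0.85²)/2 = 0.6133, so the SD is 0.783 L.
- n per group = (z_α + z_β)² × 2 × 0.6133 / 0.74².
- Two-sided α: (1.960 + 1.282)² × 2 × 0.6133 / 0.5476 = 23.5, close to the stated 23. The one-sided α that section 2.4 names gives 19.2, which rounds up to 20. That discrepancy is a separate matter.
- Drop-out: 23/0.9 = 25.6, rounded up to 26, as stated. The plan then takes 30 per arm.

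**2. Severity balance at 30:30.** Suppose K of the 60 patients are in a low-FVC group. With no strata, the number X of them in one arm is hypergeometric (60 patients, K low, 30 drawn). The arms differ by |2X − K| such patients, and a gap of 6 is 6/30 = 20 percentage points.

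For K = 24 (40%), a gap of 6 or more means X ≤ 9 or X ≥ 15:
2 × (0.0616 + 0.0236 + 0.0068 + 0.0014 + 0.0002) = 0.187.

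| Assumed low-FVC share | K | P(gap of 20 points or more) |
|---|---|---|
| 30% | 18 | 0.158 |
| 40% | 24 | 0.187 |
| 50% | 30 | 0.196 |

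The share is an assumption, but the answer varies little across this range.

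**3. The same point for a continuous baseline measure.** The difference between arm means has a standard error of √(2/30) = 0.258 SD units. A difference above 0.25 SD has probability 0.33, and one above 0.5 SD has probability 0.05.

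**4. What unequal arms would cost.** Power of the two-sided 0.05 t-test (noncentral t) on the section 2.4 inputs:

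| Split of 60 | Power |
|---|---|
| 30:30 | 94.9% |
| 26:34 | 94.6% |
| 23:37 | 93.8% |

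The loss from 30:30 to 23:37 is 1.1 points.

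**5. Why stratifying alone is not enough.** If the stratum explains 15% of the outcome variance (assumption) and is balanced by design, the true variance of the difference is 0.85 of what an unadjusted t-test uses. The type I error is then about 2 × [1 − Φ(1.960/√0.85)] = 2 × [1 − Φ(2.126)] = 0.034 instead of 0.05. A simulation with 60 patients also gave 0.034. The test becomes conservative, so the precision bought by stratifying is lost unless the analysis uses the stratum.

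**The case against.** **Chance imbalance is not bias.** Simple randomisation is valid, and the error rate of the test already allows for imbalance. This stands, and it limits the point to precision and credibility.

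**The severity figures rest on assumptions.** The low-FVC share is assumed, and the article does not state that severity predicts either primary outcome. This also stands. The probability of imbalance barely depends on the share, but its effect on the outcomes cannot be sized from the article.

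**Adjustment may be in an analysis plan that is not shown.** This is possible, and having no baseline value for exacerbations would not prevent adjustment for baseline FVC. The article does, however, name the tests it will use, and those are unadjusted.

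**A reader might infer that 30 per arm is not secured.** Independent assignment of each number would miss 30:30 with probability 0.90 and leave one arm below 26 with probability 0.25. But no section describes independent assignment. A closed list of 60 numbers, made before recruitment and divided 1:1, most naturally gives exactly 30:30 once all 60 are enrolled.

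**A reader might also infer that recruitment will stop short on a calendar date.** Section 2.3 can be read that way, but section 5.1 expects 60 participants and an end in September 2022. One year of recruitment plus 24 weeks ends around February or March 2022, so there is time to complete the sample. If recruitment did stop at 40, a figure found nowhere in the article, a gap of 8 or more on a 30:30 list would have a probability of 0.05.

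**Nor do the documents support an argument from calendar time.** This is a single-site, double-blind trial with one year of recruitment, and no time trend is identified.

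**Conclusion.** The point holds as a worthwhile and inexpensive improvement. The article chooses allocation without blocks or strata and an unadjusted analysis, so nothing it states protects against a chance difference in baseline severity between two arms of 30. The chance of a 20-point gap in low-FVC patients is about 19% at an assumed 40% share, and about 16% to 20% for shares of 30% to 50%.

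The consequence is some loss of precision and a result that is easier to dispute. How large that loss is depends on how strongly baseline FVC predicts the outcomes, which the article does not say. No bias or contradiction is shown, and the documents do not support a claim that the planned 30 per arm is unsecured. Uneven arms would in any case cost only about 1 point of power.

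**What to change.** In section 2.5, replace the completely random design with permuted blocks of randomly varying size (for example 4 and 6). The same statistical centre would generate them, with block sizes concealed from the site, stratified by one FVC% predicted cut-point fixed in advance. In section 3.6, state that both primary comparisons will be adjusted for that stratum or for baseline FVC. The two changes belong together, for the reason in step 5 of the working. If the list is already in use, the adjustment alone, fixed before unblinding, still recovers much of the benefit.

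The cost is small. FVC% is already needed to judge eligibility, so no new measurement is required, but it must be known before a number is assigned. There would be two allocation sequences instead of one. Incomplete blocks can leave the arms slightly uneven: with blocks of up to 6, at most 3 apart in each of two strata, so at worst 33:27 in 60 patients. A fully used 30:30 list avoids this, but step 4 shows that such a difference hardly affects power.

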### Diagnostic criteria

2.6

Subjects must meet the western medicine diagnostic criteria for IPF of ATS/ERS/JRS/ALAT in 2018 (Table 1)^[24]^ and the TCM syndrome diagnostic criteria of qi and yin deficiency syndrome (Table 2).^[25,26]^ The syndrome will be differentiated by 2 experienced and designated deputy physicians of TCM independently.

**Table 1 T1:** Western medicine diagnostic criteria for IPF.

Diagnostic criteria for IPF
1. Exclusion of other known causes of ILD (eg, domestic and occupational environmental exposures, CTD, drug toxicity), and either #2 or #3;
2. The presence of the HRCT pattern of UIP;
3. Specific combinations of HRCT patterns and histopathology patterns in patients subjected to lung tissue sampling.

UIP = usual interstitial pneumonia

**Table 2 T2:** The TCM syndrome diagnostic criteria for qi and yin deficiency syndrome.

Diagnostic Criteria for qi and yin deficiency syndrome
Primary symptoms:
(1) Dry cough with less phlegm;
(2) Breathless will be aggravated after moving.
Secondary symptoms:
(1) Low and weak cough voice;
(2) Fatigue and shortness of breath;
(3) Spontaneous sweating and fear of wind;
(4) Dry mouth and thirst;
(5) Night sweats.
Tongue and pulse: the tongue is tender and red with eroded fur (complete or partial peeling of the tongue coating), and the pulse is feeble and rapid or the pulse is small and weak.
More than 2 primary symptoms + 1 secondary symptom or 1 primary symptom + 2 secondary symptoms can be diagnosed as qi and yin deficiency syndrome.

TCM = traditional Chinese medicine.

### Inclusion criteria and exclusion criteria

2.7

The inclusion criteria will be: subjects aged 18 to 75, male and female; Diagnosis according to guidelines of the Idiopathic Pulmonary Fibrosis by ATS/ERS/JRS/ALAT in 2018; in line with the diagnostic criteria of qi and yin deficiency syndrome of TCM; good ability to understand and write research-related materials, and voluntary compliance with all requirements of the study; volunteer to this study and sign an informed consent.

The inclusion criteria will be: patients with acute exacerbation of IPF, those with FVC% < 50% or those with obvious pulmonary infection should be treated with anti-infection therapy; patients with chronic pulmonary diseases (such as chronic obstructive pulmonary disease, interstitial lung disease, tuberculosis and bronchiectasis); patients with severe condition of mental disorder, or laboratory test suggesting severe systemic disease (such as the dysfunction of cardio-cerebrovascular, liver and kidney, endocrine, hematopoietic system or tumor); patients who had taken glucocorticoid, immunosuppressants or antacid within 1 month; unwilling or unable to change the current treatment plan; those who are known to be allergic to Chinese herb in the experimental drug; women who are lactating, pregnant or preparing for pregnancy; participated in other clinical studies in the past half a year.

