## Abstract

**Introduction::**

With dissatisfaction of western medicine, traditional Chinese medicine becomes alternative treatment for idiopathic pulmonary fibrosis patients. The common syndrome of idiopathic pulmonary fibrosis (IPF) is qi and yin deficiency syndrome. The prescription, Modified Maimendong Decoction (MMD), is usually used for IPF patients with qi and yin deficiency syndrome. However, there is no convinced evidence for the efficacy and safety of MMD to treat IPF.

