**Methods::**

A double-blind, placebo-controlled, randomized clinical trial was put forward by us. After a 1-day run-in period, 60 eligible patients will be included in the study. These subjects will be allocated to the experiment group or control group in a 1:1 ratio. Patients in the experiment group will take MMD plus Pirfenidone capsule. At the same time, patients in the control group will receive a matched placebo plus Pirfenidone capsule. All subjects will receive 24 weeks of treatment and follow-up period. The primary outcomes are the mean change from the baseline in forced vital capacity and times of acute exacerbations at week 4, 12, 24. Secondary outcomes are the mean change from baseline in the St. George's respiratory questionnaire total score, forced expiratory volume in 1 second percentage/forced vital capacity, diffusing capacity of Carbon monoxide, brain natriuretic peptide, and curative effect of traditional Chinese medicine syndrome at week 4, 12, and 24. Any side effects of the treatment will be recorded.

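### The 1-month prior-medication exclusion leaves out Chinese herbal treatment and MMD itself, so baseline can be measured on the test formula or a related one

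*Protocol article*

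**What the plan says.** The second list in section 2.7 is plainly the exclusion list, although it is introduced as inclusion criteria. Its only time window on earlier medication is "patients who had taken glucocorticoid, immunosuppressants or antacid within 1 month". Three other entries come near the subject:

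- "those who are known to be allergic to Chinese herb in the experimental drug", which concerns allergy and not use;
- "unwilling or unable to change the current treatment plan", which concerns willingness and sets no interval;
- "participated in other clinical studies in the past half a year", which covers trial participation and not routine prescription.

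The Abstract (Methods) gives the lead-in: "After a 1-day run-in period, 60 eligible patients will be included in the study". The Abstract (Introduction) says that MMD "is usually used for IPF patients with qi and yin deficiency syndrome", which is the enrolled population, and the Discussion adds that "MMD is a common formula for the disease". Section 2.3 recruits from "respiratory clinics at the Hospital of Chengdu University of Traditional Chinese Medicine", by advertisement and doctor referral among other routes.

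Section 3.2 makes change from baseline in FVC at weeks 4, 12 and 24 a primary outcome, alongside acute exacerbations. SGRQ total score and TCM syndrome are secondary outcomes, also as change from baseline. Section 2.8 lists use of prohibited drugs as a reason for exit. The article does not print that list, and it applies after entry.

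**The concern.** The list screens for three conventional drug classes but not for recent use of the treatment under test. As written, a patient who took MMD until the day before screening meets every criterion, passes the 1-day run-in and is randomised.

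For that patient, baseline may already contain some or all of whatever MMD does. In the experimental arm little further change can be expected. In the control arm the patient moves from MMD to placebo, so the change from baseline reflects either carry-over or loss of effect on stopping. The trial asks what MMD adds to pirfenidone. With such patients included, the answer becomes a mixture of adding MMD and withdrawing it, and under carry-over the contrast is diluted. SGRQ and the TCM syndrome outcome are exposed in the same way.

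**Working it through.** **Inputs.** Section 2.4: control mean 3.07 L, SD 0.71 L; experimental mean 3.81 L, SD 0.85 L; 1:1 allocation; 90% power; one-sided 0.05; 23 per group needed, 26 after 10% drop-out, 30 recruited. Section 3.6: two-sided 0.05. The share p of recruits already on MMD or a similar formula is in neither section, so 10%, 20% and 40% are assumed.

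**The plan's own figure.** Difference = 3.81 − 3.07 = 0.74 L. Pooled SD = √((0.71² + 0.85²)/2) = 0.783 L. The section 2.4 formula gives n = 2 × (z_α + z_β)² × 0.783²/0.74². With a two-sided 0.05 this is 23.5, so the stated 23 is that value not rounded up. With the one-sided level in the text it is 19.2, or 20 per group. That mismatch is a separate matter. The two-sided level is used below because it is the one planned for analysis. Drop-out: 23/0.9 = 25.6, or 26, as stated.

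**What prior users do to the contrast.** Let E be the effect of being on MMD, and r the part of it that a prior user on placebo has lost by the visit in question (0 = full carry-over, 1 = full reversal). Any trend common to both arms cancels.

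| Patient | Change, MMD arm | Change, placebo arm | Difference |
|---|---|---|---|
| Not a prior user | E | 0 | E |
| Prior user | 0 | −rE | rE |

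Expected contrast = (1 − p)E + p·rE = E × [1 − p(1 − r)].

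- **Full reversal (r = 1):** the contrast is E whatever p is. There is no dilution and no power loss, but a share p of it comes from withdrawal. Reversal may be less complete at week 4 or 12 than at week 24.
- **Full carry-over (r = 0):** the contrast is E(1 − p).

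**Power at the carry-over extreme.** Two-sample t-test, two-sided 0.05, E = 0.74 L, SD held at 0.783 L. The non-centrality is 0.74(1 − p)/0.783 × √(n/2). With n = 30 and p = 0 that is 3.66, against a critical value of 2.002.

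| Assumed p | Contrast (L) | Power, 30 per group | Power, 27 per group |
|---|---|---|---|
| 0 | 0.740 | 94.9% | 92.6% |
| 10% | 0.666 | 90.0% | 86.6% |
| 20% | 0.592 | 82.1% | 77.8% |
| 40% | 0.444 | 57.9% | 53.4% |

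The 27 is 30 less the planned 10% drop-out. An intermediate case follows from the formula: p = 20% with half the benefit lost (r = 0.5) gives 0.74 × (1 − 0.20 × 0.5) = 0.666 L, the same as the 10% row.

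**The case against.** - **Condensed article.** The article refers to prohibited drugs without listing them, and the full protocol may do so. That stands for the list, so nothing is claimed about its contents. It does not answer the point about section 2.7, where the article prints a specific window with specific drug classes. A list of drugs barred during the trial also would not by itself fix an interval before baseline.

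- **Already handled.** Excluding patients who cannot or will not change their treatment plan may well mean that herbal users stop at entry. That narrows the gap but does not close it: stopping at entry leaves baseline measured on the herb, and it creates the withdrawal case in the control arm.

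- **Internal validity.** A reader might infer that the omission biases the trial in favour of MMD. The document does not support that. Prior use comes before a randomised, blinded allocation and is balanced in expectation, and under carry-over the effect is dilution. Only chance imbalance is possible, with 30 per group and no stratification described.

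- **One extreme.** A reader might also take the powers above as the expected loss. They are not. They need a prior user on placebo to keep the whole benefit for 24 weeks, which nothing in the article establishes. With full reversal the loss at week 24 is zero.

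- **Unknown p and a different formula.** The remarks on common use are background statements and not prevalence data, and recruitment also uses advertisement and referral. The trial product (section 2.9) is a specific granule. It lacks the rice and jujube of the classical decoction in the Introduction and adds three other herbs. Prior use of the classical decoction is therefore use of a related formula, not of the test product. This limits how much can be said about size, but the criterion is still absent.

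**Conclusion.** The gap in section 2.7 is certain on the text: recent use of MMD or another Chinese herbal treatment is neither excluded nor washed out, and the run-in is 1 day. The article's own account of how MMD is used, and where patients are recruited, makes such entrants plausible.

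The consequence is a range. At one end, the week-24 contrast is numerically about unchanged but partly measures withdrawal. At the other, it is diluted to 1 − p of its value, with power at 30 per group of 90%, 82% and 58% at assumed p of 10%, 20% and 40%, against 95% at p = 0. These figures rest on the section 2.4 difference and SDs taken at face value and on an assumed p. Neither p nor the degree of reversibility is in the article. The harm is possible loss of power and a blurred question, not a systematic tilt towards MMD. The change is worth making because it is cheap, and the Discussion already concedes that the sample may be too small.

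**What to change.** In section 2.7, extend the existing prior-medication exclusion to recent use of MMD, Maimendong decoction and other Chinese herbal treatment for lung disease. The sponsor should choose the interval and justify it; the 1 month set for the other drug classes need not carry over. State that baseline FVC, SGRQ and TCM syndrome are measured after that interval. Record prior herbal use at baseline, so that its frequency and its balance between arms can be reported.

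The cost is a line or two of eligibility text and one item on the case report form. Some patients at a TCM clinic would become ineligible or have to wait, so recruitment would be slightly slower.
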